### **Study design**

Each subgroup includes five participants and each one constitutes a separate research study that follows a concurrent multiple baseline design across subjects, designed according to the 'What Works Clearinghouse' criteria for single case studies (50). During the experimental procedure, all participants will begin the study with the baseline phase at the same time while the intervention phase is introduced staggered across patients and time (see Figure 1). The intervention will be introduced systematically in one patient while baseline data collection continues in the others without any intervention. The cause-effect inference can be clearly verified by the staggered duration through separate baseline phases (51). Subsequently, if the intervention is the sole cause of improvement in participants' conditions, the proposed outcome measures will not change for the participants that remain in the baseline phase but will be improved only for those in the intervention phase.

### **Data Acquisition of Outcome Measures**

#### **Primary Outcome Measures**

We will assess the corticospinal plasticity using single pulse TMS in the neurophysiology lab of the Cyprus Institute of Neurology and Genetics, in all phases (see Figure 1). Using electromyography (EMG) signals, we will analyze bilateral cortical excitability and bilateral CMCT

to determine corticospinal plasticity and therefore to test the primary hypothesis. The rMT and the MEP amplitude of Abductor Pollicis Brevis muscle will define cortical excitability, while we will use the MEP latency to calculate the CMCT. During all neurophysiological assessments, participants will be in a relaxed sitting position in a comfortable chair with feet touching the floor and both arms will be placed on cushioned armrests and with the head rested on a cushion. To ensure methodological consistency, we will collect all data by performing the same methodological procedures for both conditions (i.e., cortical excitability and CMCT) bilaterally (one side per assessment), across participants and across all time points.

### **TMS assessment**

Following TMS recommended guidelines concerning safety and experimental conditions (59,60), we will assess bilateral cortical excitability and bilateral CMCT. We will apply TMS single pulses (61) via figure-eight coil (C-B60; inner diameter: 35mm, outer diameter: 75mm), connected to the MagPro R20 (MagVenture User Guide, United Kingdom edition, MagVenture A/S, Denmark). For the TMS procedures, we will first find the optimal stimulation site (i.e., hot-spot), next we will determine the rMT, and then apply a bout of single pulses using suprathreshold stimulation. To determine hot-spot (i.e., the spot in which the largest response of the target muscle is elicited), we will deliver single pulses at low intensities (e.g., ~20% maximum stimulator output) and gradually increase it by 5%, maximum stimulator output until we will reach the intensity that will elicit three consecutive MEPs with peak-to-peak amplitude greater than 50mV (62,63). Then, we will determine the rMT of the target muscle which is the minimum stimulation intensity needed to produce MEPs of the target muscle and it is defined by the hot-spot. To identify the rMT of the Abductor Pollicis Brevis muscle, we will employ an adaptive threshold-hunting method, the Motor Threshold Assessment Tool (MTAT 2.0) (64) (available at <http://clinicalresearcher.org/software.htm>). The specific method has the advantage of speed without losing accuracy when compared to the relative-frequency methods based on the Rossini–Rothwell, although both methods have similar precision (65). Then, to quantify the MEP-derived measures of interest (i.e., MEP amplitude, latency), we will apply 25 suprathreshold stimuli (66) at 120% of the rMT (67).

### **Secondary outcome measures**

All clinical assessments will be performed in all phases (see Figure 1) in the physiotherapy unit of the CING and reliability of the measures will be assessed by having two trained physiotherapists, blinded to the research study, independently record the measures of each outcome.

#### **Mini Balance Evaluation Systems Test (Mini-BESTest).**

The Mini-BESTest (68) it is a shorter version of the Balance Evaluation Systems Test (BESTest) (69). This test measures dynamic balance, functional mobility, and gait in neurologic patients, including pwMS. The Mini-BESTest consists of 14 items, including four of the six segments (anticipatory postural adjustments, sensory orientation, reactive postural control and dynamic gait) from the BESTest. The Mini-BESTest should be scored out of 28 points to include 14 items that are scored from zero to two.

### **Six Spot Step Test (SSST)**

The SSST (70) is a timed walking test that involves kicking over a number of targets placed along a 5m-path in which rely to some extent on vision and cognition. The SSST is measured in the time domain, replicates a complex range of sensori-motor functions, part of which are lower limb strength, spasticity, coordination, as well as balance. We will perform the specific test as it is described by Nieuwenhuis et al (2006) (70) and we will record the mean time of the four runs as the final test result (71).

### **Action Research Arm Test (ARAT)**

The ARAT (72) is a 19-item observational measure used by physiotherapists and other health care professionals to examine upper extremity performance i.e. coordination, dexterity and functioning. Items covering the ARAT are categorized into four subscales (grasp, grip, pinch and gross movement) and arranged in order of decreasing difficulty, with the most difficult task examined first, followed by the least difficult task. The patient is sitting comfortable in front of a stable desk performing each task and the performance is rated on a four-point scale, ranging from 0 (no movement) to 3 (movement performed normally). We will record the total score for each upper limb separately as the final test result.

### **Isometric Dynamometer**

The isometric muscle force of the major muscle groups will be assessed with the use of the muscle controller (Kinvent Biomechanique, Montpellier, France), which is a dynamometer used in the evaluation and rehabilitation of muscle strength that provides real time biofeedback. The patient lies (supine or prone) on a therapeutic bed and the physiotherapist, with the use of the muscle controller, holds against the patient's limb as the patient exerts a maximal force. The physiotherapist counters the force (make test), or tries to break the contraction (break test) and the data will be collected and stored using the KFORCE APP (Kinvent Biomechanique, Montpellier, France). Shoulder flexors, extensors, rotators, horizontal adductors and abductors, adductors and abductors, elbow flexors and extensors are the major muscle groups which will be evaluated (73). ). Shoulder flexors, extensors, rotators, horizontal adductors and abductors adductors and abductors, elbow flexors and extensors are the major muscle groups which will be evaluated. A separate value for each muscle group will be recorded in order to be used in the visual and statistical analysis.

### **Symbol Digit Modalities Test- Oral form (SDMT)**

The SDMT - oral form (74) assesses the IPS. During the test, the participant will be given two minutes to orally match symbols with digits as quickly as possible. The key (specifying which symbols are assigned to which numbers) will be located at the top of a computer screen. The physiotherapist who is responsible for all clinical assessments will record the participant's responses directly on the computer screen. The physiotherapist instructs the participants that each symbol is paired with a number and they are arranged across the row. Afterword, the participant is instructed how to response orally in the row without the numbers. For example, the symbol "O", it is matched with the number 6, so the participant would say "6"; this next symbol "X", is paired with the number 8, so the participant would say "8". The participant will have the possibility to correct a mistake and continue, alongside the physiotherapist should strike through the items on which the participant makes errors. The score is obtained by subtracting the number of errors from the number of items completed in two minutes.

## **Questionnaire**

The questionnaire which will be used is published in English, but all questions will be orally translated to Greek from the physiotherapists who will performed all clinical assessments and every response will be recorded at the participants' presence.

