pushups, TRX) (56). The intervention phase for each participant consists of 12 consecutive weeks in which the proposed protocol will be performed three times per week, for 30-60 minutes each session, in respect of individual levels of fatigue. However, the duration and the intensity of the exercises will be designed considering previous literature (37,57) and recommendations (58). Additionally, for each participant we will perform several neurophysiological and clinical assessments during baseline, intervention and follow up phases. The neurophysiological assessments include evaluation of corticospinal plasticity via TMS (27,30). Corticospinal plasticity characterized via certain TMS-specific neurophysiological measures including resting MT (rMT), motor-evoked potential (MEP) amplitudes and the CMCT (30). Moreover, clinical assessments will be gathered regarding motor skills (i.e., walking, balance, strength, upper limb dexterity) and cognitive functions (i.e., IPS), as well as a subjective questionnaire will be provided to the participants related to fatigue. Age, gender and disease duration since diagnosis will be collected as descriptive measures.

The benefits that all participants will gain are the systematic evaluation of their clinical condition for a long period of time, as well as their participation for a long time in an exercise program which will keep them physically active.

The expected results of this research are:

- 1) Improvement of motor functions (gait, balance, strength, upper extremity functionality).
- 2) Improvement cognitive functions (information processing speed).
- 3) Possibility to increase the plasticity index in both cerebral hemispheres, which means that each patient will have a much better prognosis in a possible relapse, due to the nature of the disease, as well as a qualitative recovery in a such situation.
- 4) Potential reduction of the CMCT in which there will be an improvement in the control of several motor functions, mainly of the upper limbs.
- 5) All participants will also benefit from a number of clinical evaluations and exercise sessions, which are much more in quantity than what they are funded throughout the General Health System.

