## **Modified Fatigue Impact Scale (MFIS)**

It is a short questionnaire which requires the participants to describe the effects of fatigue during the past four weeks (75). The MFIS consists of 21 questions which are subjectively rated from "0" (low rate) to "4" (high rate) and it is also divided into three subscales (i.e., physical, cognitive, and psychosocial). The higher the score is, the greater is the impact of fatigue in individual daily life. Although, to describe fatigue level the Fatigue Severity Scale is more commonly used, we decided not use it because it describes severe fatigue. Therefore, we will use the Modified Fatigue Impact Scale as the description of participants' attribution of functional restrictions to fatigue symptoms.

The intervention protocol and all clinical assessments will be performed in the physiotherapy unit of the CING and reliability of the measures will be assessed by having two trained physiotherapists, blinded to the research study, independently record the measures of each outcome. Also, neurophysiological assessments will be executed and recorded from the experimenters who are trained in the use of the TMS equipment regarding the needs of the proposed study, in the neurophysiology lab of the CING, in separate days from those of the clinical assessments. During the follow-up phase both clinical and neurophysiological assessments will be performed at the same day for each participant. To note, each participant has to complete at least 27 (75%) out of 36 sessions in order to be included in the final data analysis (76). All of the measures are to be administered by the clinical research team member (senior physiotherapist) under the supervision of the project coordinator. All data and personal information collected from the study will be stored safely without being shared between researchers at the premises of CUT and CING. Five years after data collection the measurements and records will be safely destroyed.

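### The MFIS, the only patient-reported outcome, is translated aloud into Greek with no fixed wording, which adds noise to the within-person phase comparison and leaves room for a spurious individual-level effect

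*Protocol*

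**What the plan says.** The Questionnaire section of the Protocol sets out the procedure: "The questionnaire which will be used is published in English", and "all questions will be orally translated to Greek from the physiotherapists who will performed all clinical assessments". Answers are recorded with the participant present. No written Greek version, script or rule on wording appears there or elsewhere.

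The instrument is the MFIS: "The MFIS consists of 21 questions which are subjectively rated" from 0 to 4. Participants and methods mentions one questionnaire only ("a subjective questionnaire will be provided to the participants related to fatigue"). Every other outcome is a TMS measure or a performance test.

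Secondary outcome measures places the clinical assessments in all phases. Clinical measures analysis averages the MFIS within each phase and takes differences between the phase means. Statistical analysis adds individual-level effect sizes, with each outcome tested separately at a two-sided 0.05 level.

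The Protocol is not consistent on who puts the questions:
- Secondary outcome measures, repeated under the MFIS heading, plans for "having two trained physiotherapists, blinded to the research study, independently record the measures of each outcome".
- The MFIS section also says that a single team member, a senior physiotherapist, administers all measures. The design and setting text before Participants and methods says the same.
- The Symbol Digit Modalities Test section refers to one physiotherapist responsible for all clinical assessments.
- The Questionnaire section uses the plural.

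**The concern.** This is a procedure that the Protocol fixes, not a detail left for a statistical analysis plan. Each participant is their own control, so a change in score between phases can be read as a change in fatigue only if the questions stayed the same. An unscripted oral translation of 21 subjectively rated items does not ensure that, even if one person translates throughout.

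Two kinds of harm are possible:
- Unsystematic variation from visit to visit widens the scatter within each phase. The effect sizes shrink and a real change in fatigue becomes harder to see.
- A lasting change (a translator settling on a different phrasing, or a change of assessor) shifts the level of the series. If it falls near the participant's move from baseline to intervention, the planned tools could read it as an effect. In particular, the immediacy check compares the last three points of one phase with the first three of the next.

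**Working it through.** The Protocol gives no figure for measurement error in the MFIS, so there is none to reproduce. The check has two parts.

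**1. Do the stated safeguards fix the wording?**
- *Blinding* (Secondary outcome measures; MFIS section): limits steering by an assessor who knows the phase. It does not stop phrasing from drifting.
- *Inter-assessor agreement* of at least 0.8 on at least 20% of data points (Visual analysis): the text does not say whether the two recorders share one interview. If they do, they hear the same answer to the same spoken question and will agree whatever the wording was. If each interviews separately, the check could show differences between translators, but not drift that both share.
- *Checklist and assessor preparation* (Treatment Fidelity): general provisions. Wording cannot be checked against a reference text when none exists.
- *Staggered starts* (Study design): a false functional relation would have to recur at each participant's own start. This protects the pattern across the five cases, but less so a single participant's effect size.

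**2. How large could it be?**

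Inputs from the Protocol: 21 items scored 0 to 4, so the maximum is 21 × 4 = 84; five intervention time points (stated for the TMS measures); two-sided 0.05.

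Assumptions not in the Protocol: five baseline visits, visit-to-visit MFIS SD of 4, 6 or 8 points, no true effect, and a wording shift k of 2, 4 or 6 points (2/84 = 2.4%, 4/84 = 4.8%, 6/84 = 7.1% of the range). A two-sided t-test of baseline against intervention visits within one participant stands in for the planned individual-level analysis. There were 20,000 simulated participants per setting.

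Formulas: for wording that moves the score by +k or −k at random at each visit, the standardized effect is multiplied by SD/√(SD² + k²). For a lasting shift at the phase change, the spurious standardized difference is d = k/SD. Example with SD 6 and k 4: multiplier 6/√(36 + 16) = 0.83; spurious d = 4/6 = 0.67.

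| SD | k | False positives: fixed wording | Random at each visit | Lasting, at phase change | Lasting, at a random visit | Multiplier of d (random) | Spurious d (at phase change) |
|---|---|---|---|---|---|---|---|
| 4 | 2 | 4.9% | 4.8% | 10.6% | 6.7% | 0.89 | 0.50 |
| 4 | 4 | 5.1% | 5.0% | 29.3% | 12.3% | 0.71 | 1.00 |
| 4 | 6 | 5.0% | 5.2% | 55.5% | 19.5% | 0.55 | 1.50 |
| 6 | 2 | 5.1% | 5.1% | 7.7% | 5.9% | 0.95 | 0.33 |
| 6 | 4 | 4.9% | 5.0% | 15.8% | 8.5% | 0.83 | 0.67 |
| 6 | 6 | 4.8% | 5.4% | 28.3% | 12.0% | 0.71 | 1.00 |
| 8 | 2 | 5.1% | 5.0% | 6.5% | 5.6% | 0.97 | 0.25 |
| 8 | 4 | 5.0% | 5.0% | 10.5% | 6.8% | 0.89 | 0.50 |
| 8 | 6 | 5.0% | 5.4% | 18.4% | 8.9% | 0.80 | 0.75 |

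Random variation costs precision and leaves the error rate alone. A false effect needs a lasting change, and it is largest when that change coincides with the change of phase. With fixed wording, k is 0 and the rate stays at about 5%.

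**The case against.** The case for leaving this alone is that the MFIS is one of several secondary outcomes, that the recording physiotherapists are meant to be blinded, that assessors are prepared and monitored, and that the staggered design makes a chance shift unlikely to line up with five different start dates. All of this stands as a reason to rank the point modestly. None of it supplies a fixed Greek text.

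Three stronger readings are tempting, and the documents do not support them:
- *A reader might infer that oral translation will in itself imitate an intervention effect.* Visit-to-visit variation does not. Only a lasting change does so, chiefly one near the phase change, and the consistency review across staggered participants works against it.
- *A reader might infer that different physiotherapists take turns at translating.* The Protocol contradicts itself on this, and several statements point to one administrator. Variation between visits remains possible with one person; variation between assessors depends on how the contradiction is resolved.
- *A reader might infer that five years of recruitment worsens the problem.* The comparison is within person, and each subgroup of five is treated as its own study, so differences in wording between people recruited years apart do not enter it.

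**Conclusion.** The concern holds in a limited form. The Protocol prescribes an unscripted oral translation of its only patient-reported outcome and then compares the score within person between phases. The main expected harm is noise: the standardized effect falls to between 0.55 and 0.97 of its value under the assumptions above. The less likely harm is a spurious individual-level effect: a false-positive rate of 6.5% to 56% if a lasting change coincides with the phase change, and 5.6% to 19.5% if it falls at a random visit. These ranges rest on assumed visit numbers, SDs and shifts and on a simple t-test. They show direction and rough size and do not predict what this trial will see. The existing safeguards lower the risk without removing its source. The TMS primary outcomes and the performance tests are untouched, so no primary conclusion changes.

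**What to change.** In the Questionnaire section, replace the oral translation with one written Greek MFIS text prepared before the first participant: a validated version if one is available, otherwise a forward and back translation. State that participants complete it themselves or have it read to them verbatim at every visit.

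Reconcile the design and setting text, Secondary outcome measures, the Symbol Digit Modalities Test section, Questionnaire and the MFIS section on whether one or two physiotherapists administer the scale.

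The cost is a one-off translation of 21 items and a few sentences of Protocol text. Visits, sample size and analysis stay as they are. The only downside is a small preparation effort before the start.

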## **Modified Fatigue Impact Scale (MFIS)**

It is a short questionnaire which requires the participants to describe the effects of fatigue during the past four weeks (75). The MFIS consists of 21 questions which are subjectively rated from "0" (low rate) to "4" (high rate) and it is also divided into three subscales (i.e., physical, cognitive, and psychosocial). The higher the score is, the greater is the impact of fatigue in individual daily life. Although, to describe fatigue level the Fatigue Severity Scale is more commonly used, we decided not use it because it describes severe fatigue. Therefore, we will use the Modified Fatigue Impact Scale as the description of participants' attribution of functional restrictions to fatigue symptoms.

The intervention protocol and all clinical assessments will be performed in the physiotherapy unit of the CING and reliability of the measures will be assessed by having two trained physiotherapists, blinded to the research study, independently record the measures of each outcome. Also, neurophysiological assessments will be executed and recorded from the experimenters who are trained in the use of the TMS equipment regarding the needs of the proposed study, in the neurophysiology lab of the CING, in separate days from those of the clinical assessments. During the follow-up phase both clinical and neurophysiological assessments will be performed at the same day for each participant. To note, each participant has to complete at least 27 (75%) out of 36 sessions in order to be included in the final data analysis (76). All of the measures are to be administered by the clinical research team member (senior physiotherapist) under the supervision of the project coordinator. All data and personal information collected from the study will be stored safely without being shared between researchers at the premises of CUT and CING. Five years after data collection the measurements and records will be safely destroyed.

## **Analysis plan**

To investigate possible effects of our protocol we will follow recommended guidelines (77), in which we will perform a separate analysis for each of the outcome measures, in all experimental phases (i.e., baseline, intervention and follow up). We will perform a visual analyses first, in order to determine whether there is a functional relationship between the intervention and the outcome measures, and secondly, we will perform a quantitative analysis methods to evaluate the magnitude of the intervention effect, provided there is evidence from the visual analyses (77). We will perform all neurophysiological and clinical assessments to each participant according to the number of data points during each phase (i.e., baseline, intervention, follow up) (see Figure 1).

